**Figure 1 figure1:**
[figure not shown]
CONSORT (Consolidated Standards of Reporting Trials) flow diagram for the health action process approach-multiple sclerosis (HAPA-MS) randomized controlled trial.

### Data Collection

Study assessments will be conducted at baseline, postintervention (ie, after the 8-week intervention), 3 months postintervention, 6 months postintervention, and an optional follow-up at 12 months postintervention (Figure 2). Throughout the testing phase, participants will be provided with prepaid posting labels and packages for easy access and hassle-free delivery of study material.

**Figure 2 figure2:**
[figure not shown]
A flow diagram of data collection time points for the health action process approach-multiple sclerosis (HAPA-MS) randomized controlled trial.

#### Baseline Demographics

During the screening process, basic demographic information will be collected, including age, gender, sex, ethnicity, level of education, income, and employment status. We will also collect additional information, including the type of MS, MS diagnostic tests, MS diagnosis year, and availability of PA-related resources around the individual. We will use this information to further enhance our knowledge regarding factors that may be related to supporting a physically active lifestyle.

#### PA Measures

ActiGraph (wGT3X-BT; ActiGraph LLC) accelerometers will be used to collect PA data during the data collection time points. Participants will be asked to wear the accelerometer around their waist on the nondominant side for 7 days and complete the accelerometer log sheet, including time stamps of wear time. ActiGraph accelerometers were deemed fit for collecting step count data. One study has shown that ActiGraph accelerometers accurately measure steps during moderate and fast walking speeds by both people with MS and control groups. Motl et al [54] indicated a slight underestimation of step count during slow-paced walking using an accelerometer with both people with MS and control groups. Given this, this study will encourage the intervention group participants to keep an optional PA log from the start of the intervention until the end of the study. The log includes recording information on the type, duration, frequency, and intensity of activities performed throughout the day.

#### Questionnaire Measures

The study will use the questionnaires and measures described in the following paragraphs to collect data regarding components of HAPA, PA, functionality, pain, fatigue, anxiety, and depression.

The Abbreviated Late Life Function and Disability Inventory has 2 subscales: function and disability. It has 15 items about the difficulty and frequency of performing physical activities rated on a 5-point Likert scale. Cronbach α values are 0.58 to 0.85 [55].

The McGill Pain Questionnaire has a 15-item adjective checklist that captures sensory and affective dimensions of pain experienced during the past 4 weeks. The items are rated on a 4-point scale [56]. Its Cronbach α value is 0.88 [57].

The Fatigue Scale for Motor and Cognitive Functions has 20 items (10 for cognitive and 10 for physical fatigue) rated on a 5-point scale. Its Cronbach α values are 0.91 to 0.95. Cutoff values are available to classify patients as mildly, moderately, or severely fatigued [58].

The Hospital Anxiety and Depression Scale has 14 items (7 for anxiety and 7 for depression) rated on a 4-point scale. The depression (*r*=0.70, *P*<.001) and anxiety (*r*=0.74, *P*<.001) subscales are correlated with psychiatric ratings [59]. Cronbach α values are 0.82 to 0.83 [57].

The HAPA battery of risk perception includes the subscales of Disease Threatening, Exam Result Threatening, Risk to Self, Risk to Others, Relative Vulnerability, and Perceived Severity. Each of these subscales has 10 to 13 items based on secondary health conditions in people with MS that are rated on a 7-point scale. Cronbach α values are 0.92 to 0.94 [37]. The HAPA battery of exercise benefits includes the subscales of Exercise Influence on Health Problems (13 items) and Outcome Expectancy (14 items). Cronbach α values are 0.79 to 0.93 [37]. The HAPA battery of motivation includes the subscales of Intention to Do PA (8 items) and Motivational Self-Efficacy (3 items). Cronbach α values are 0.90 and 0.85, respectively [37]. The Cognitive and Behavioral Process of Change Scale has 30 items (15 for the cognitive subscale and 15 for the behavioral subscale) rated on a 5-point scale. Cronbach α values are 0.67 to 0.86 [60]. The Exercise Goal Setting and Planning Scale has 20 items (10 for the goal setting subscale and 10 for the planning subscale) rated on a 5-point scale. Cronbach α values are 0.89 and 0.87, respectively [61]. The Barriers to Health Promotion Activities Scale has 18 items rated on a 4-point scale. Its Cronbach α value is 0.82 [62]. The PA-specific Social Provisions Scale has 24 items rated on a 4-point scale. Its Cronbach α value is 0.89 [57,63]. The Physical Activity Self-Regulation Scale has 12 items rated on a 5-point scale. Cronbach α values are 0.79 to 0.94 [64]. The HAPA battery of PA volition includes the subscales of PA Action Planning (5 items), PA Coping Planning (4 items), Recovery Self-Efficacy (3 items), and Coping Self-Efficacy (13 items) rated on a 4-point scale. Cronbach α values are 0.91 to 0.97 [37].

PA and sedentary behavior will also be assessed using patient-reported scales, that is, the Physical Activity Scale for Individuals with Physical Disabilities (PASIPD) [65] and GLTEQ. Cronbach α values for the PASIPD are 0.37 to 0.65 and for the GLTEQ are 0.46 to 0.94 [65-67].

### Statistical Analysis

Research assistants will monitor survey completion and accelerometer data sufficiency. When participants return their survey and accelerometers, research assistants will check whether the participants have not responded to the entire survey. If there are missing responses, research assistants will email or call the participants to encourage them to respond to the missing items. The participants will be reminded twice, once each at 2 and 4 weeks, after they return the survey. If their accelerometers do not record valid data, research assistants will contact the participants and ask if they are willing to wear it for 7 days. After those attempts, when we curate the data, we will code missing data as 999.

Our analytic approach will use an intention-to-treat framework, and mixed models will yield unbiased results if the data are “missing at random” [68]. Additional sensitivity analyses will be performed to test for informative dropouts [68]. We will apply pattern-mixture models by stratifying our data by dropout patterns and fitting separate regression models to strata [68]. SPSS 26 (IBM Corp) will be used to conduct descriptive analyses (means, standard deviations), chi-squared tests, independent *t* tests, paired *t* tests, repeated measures ANOVAs, and 2-way (any 2 factors of conditions, disability severity levels, and time) and 3-way (conditions × disability severity levels × time) mixed model ANOVAs. Conditions and disability severity levels are between-subjects factors. Time is a within-subjects factor. We will use 2-way and 3-way ANOVAs to compare measured variables of the intervention and control groups. The significance level is set at .05. We will examine effect sizes of partial ηp2 (0.01, 0.06, and 0.14 as small, moderate, and large effect sizes, respectively) and Cohen *d* (0.20, 0.50, and 0.80 as small, moderate, and large effect sizes, respectively) [69]. We hypothesize that the intervention group will have stronger motivation and self-regulation, more PA, and better health conditions than the control group.

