### Objectives

The proposed study aims to assess the preliminary effectiveness of an online intervention to promote PA by people with MS (hereafter called an HAPA-MS intervention). We hypothesize that the intervention group will demonstrate (1) higher scores of HAPA components (see the Measures section) and (2) higher frequency, duration, and intensity of PA engagement immediately following the intervention and 6 months or longer after the intervention than the control group.

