## Results

The study was funded in April 2018. We conducted peer coach selection interviews from July 2018 through October 2018. Peer coaches codeveloped and evaluated each module of the online program from November 2018 through January 2020. We iteratively revised the modules based on the peer coaches’ feedback. During the pandemic, participants preferred to discontinue the study. The modules also had to be migrated from the Moodle system to a new online learning system, Canvas, in 2022 due to changes in the university’s online learning system.

We invited peer coaches to review the accessibility of online modules in fall 2022. We finalized the module accessibility and trained peer coaches on how to use the online modules in December 2022. Since February 2023, we have recruited 50 participants to the trial who have been assigned to the intervention group (n=25) or control group (n=25). During the follow-up stage, 3 participants dropped out of the intervention group, and 4 participants dropped out of the control group. Enrollment ended in 2024, and data collection is expected to conclude by December 2025, with results anticipated to be published in January 2026.

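### Intention-to-treat and missing-at-random validity are claimed for mixed models, but the arm comparison is described as a classical ANOVA, which drops anyone missing an included visit

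*Protocol article*

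**What the plan says.** All the statements on method stand in one paragraph of the protocol article (Methods, Statistical Analysis).

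- The framework: "Our analytic approach will use an intention-to-treat framework, and mixed models will yield unbiased results if the data are" missing at random. Pattern-mixture models are added as sensitivity analyses for informative dropout.
- The procedures to be run in SPSS 26 include "independent *t* tests, paired *t* tests, repeated measures ANOVAs", followed by 2-way and "3-way (conditions × disability severity levels × time) mixed model ANOVAs".
- The procedure assigned to the arms: "We will use 2-way and 3-way ANOVAs to compare measured variables of the intervention and control groups".
- Condition and disability severity are between-subjects factors and time is a within-subjects factor. Partial eta squared and Cohen d are the effect sizes.

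Three other places bear on the point. Data Collection lists baseline, post-intervention, 3 months, 6 months and "an optional follow-up at 12 months postintervention"; the Abstract lists 12 months with the other visits and does not mark it optional. Objectives hypothesises a benefit "immediately following the intervention and 6 months or longer after the intervention than the control group". Results reports 25 participants per arm, of whom "3 participants dropped out of the intervention group, and 4 participants dropped out of the control group".

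**The concern.** Validity under missing at random belongs to a likelihood-based model fitted to all available observations. It does not pass to other procedures that share part of the name. A classical repeated-measures ANOVA needs a complete row for each participant, so one missing visit removes all of that person's data. The people analysed are then those who completed every included visit, which is not the randomised set.

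If the paragraph means a classical ANOVA, its assurance of unbiasedness is attached to a method that is not the one producing the arm comparison. Readers would then give complete-case results a credibility they have not earned. The optional 12-month visit could make this worse, because declining it might also discard observed post-intervention, 3-month and 6-month data.

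**Working it through.** **1. Which model is described?**

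| Feature in the article | Likelihood mixed model | Classical split-plot ANOVA |
|---|---|---|
| Label mixed model ANOVA | possible | possible |
| Between- and within-subjects factors | not specific | standard description |
| Partial eta squared | not its usual output | standard output |
| Power analysis for a within-between interaction (Sample Size section) | not specific | matches |
| Random effect, covariance structure or likelihood estimation | none named | not needed |

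The description points to the classical ANOVA. Only the label points the other way.

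**2. Who is lost under each listed procedure?**

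- Independent t test at one visit: those missing at that visit.
- Paired t test: those missing at either of the two visits.
- Classical repeated-measures or split-plot ANOVA: those missing at any included visit.
- Likelihood mixed model: nobody who has any outcome data.

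**3. Counts.** The inputs are 25 + 25 enrolled and 3 + 4 dropouts (Results).

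- Dropout: 7/50 = 14% (3/25 = 12% and 4/25 = 16%).
- Remaining: 22 + 21 = 43.
- The article gives no uptake for the 12-month visit. If that visit were a level of the time factor, and the 43 were otherwise complete:

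| Assumed uptake | Complete cases | Share of 50 |
|---|---|---|
| 90% | 20 + 19 = 39 | 78% |
| 70% | 15 + 15 = 30 | 60% |
| 50% | 11 + 10 = 21 | 42% |

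**4. Precision, as a rough guide.** The article's own figure reproduces. A one-sided two-sample t test with alpha 0.05 and power 0.80 (noncentral t) needs 30 per group at d=0.65 and 26 at d=0.70. The same formula at smaller sizes gives:

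| Analysed | Power, d=0.65 to 0.70 |
|---|---|
| 60 (planned) | 0.80 to 0.85 |
| 50 (enrolled) | 0.73 to 0.79 |
| 43 | 0.67 to 0.73 |
| 39 | 0.64 to 0.69 |
| 30 | 0.54 to 0.59 |
| 21 | 0.42 to 0.46 |

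These are t-test figures, not the power of the ANOVA interaction. The step from 60 to 50 is a recruitment shortfall and not part of this point.

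**5. Does the missing-at-random property carry over?** A large-sample simulation used three visits, correlation 0.5 between visits, and a true difference of 0.65 SD after baseline. Attendance at the last visit depended only on the previous score: logit P = 0.8 + slope × score. About 66-77% attended. Data are missing at random by construction.

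| Slope, intervention / control | Complete-case difference | Likelihood-type estimate |
|---|---|---|
| 0 / 0 | 0.65 | 0.65 |
| 1 / 1 | 0.61 | 0.65 |
| 1 / 0 | 0.75 | 0.65 |
| 1 / -1 | 0.89 | 0.65 |

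The property holds for the likelihood-type estimate and fails for complete cases in three of the four settings.

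**6. Is the direction known?** Take the 6-month contrast restricted to 12-month attenders. Suppose an arm keeps 90% of those above its own 6-month median and 60% of those below. The half-normal mean is 0.798 SD, so that arm's mean shifts by 0.798 × (0.9 - 0.6)/(0.9 + 0.6) = 0.16 SD.

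- Selection in the intervention arm only: +0.16 SD, which is 0.16/0.65 = 25% of the planned d=0.65.
- The same selection in both arms: 0.16 - 0.16 = 0.
- Selection in the control arm only: -0.16 SD.

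The retention rates are invented, so the sign and size are open.

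**The case against.** The best defence is the label. The paragraph credits mixed models with validity under missing at random and then calls its 2-way and 3-way analyses mixed model ANOVAs. If a likelihood model such as SPSS MIXED is meant, the arm comparison is valid under missing at random. This stands as an ambiguity. It does not settle the matter, because the rest of the description fits the classical ANOVA, and the listed repeated measures ANOVAs and t tests lie outside the claim on either reading.

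Missing data are not ignored. Reminders at 2 and 4 weeks, requests to wear the accelerometer again and pattern-mixture models are all planned. The pattern-mixture models are only sensitivity analyses, however, and they leave the main comparison as it is. With 3 and 4 dropouts per arm, separate regressions by dropout pattern can hardly be estimated.

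The article is a condensed document. Covariance structure, estimation method and degrees of freedom may properly sit in an analysis plan that is not shown, and their absence is no fault. The fault lies in what the paragraph itself states.

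A reader might infer that the 6-month contrast will be estimated only in people who return at 12 months. The article does not support that: it does not say which visits form the time factor, its power example uses 3 times, and an optional visit may be analysed separately. Nor do the t tests share this problem. An independent t test at 6 months loses nobody for skipping 12 months, and the article does not assign the arm comparison to t tests.

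**Conclusion.** The point holds in a bounded form. The paragraph claims intention-to-treat and validity under missing at random, yet describes its arm comparison in the terms of a method that has neither property once visits are missing. That the classical ANOVA is meant is the more likely reading, not a certainty.

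The firm figure is the 14% (7 of 50) already lost, and it does not depend on the 12-month visit. The range of 21-39 analysed out of 50 rests on three assumptions: that 12 months is a level of the time factor, that uptake is 50-90%, and that the remaining 43 are otherwise complete.

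A reader might go further and infer that the treatment effect will be inflated by a known amount. The article does not support this. Reported dropout is nearly balanced, and bias can be upward, downward or zero depending on who is missing in each arm. What is established is that the assurance of unbiased results does not extend to a complete-case ANOVA.

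**What to change.** Make the arm comparison one likelihood-based linear mixed model, for example SPSS MIXED with visit as a categorical factor, on every randomised participant with any outcome data. Read the arm contrast at post-intervention and at 6 months. State which visits enter the model. Treat the 12-month contrast as exploratory, so that declining that visit removes no earlier data. Use this model in place of the ANOVAs for comparing arms, and keep the pattern-mixture work as sensitivity analysis.

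If a likelihood model was meant all along, say so and drop the ANOVA wording. Narrowing the hypothesis from 6 months or longer to 6 months is optional: a 12-month assessment exists, so the present wording is not contradicted. Estimation and degrees-of-freedom details can stay in the analysis plan.

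The cost is analysis wording and a weaker 12-month claim. The software stays the same and no new data are needed. The change should be made before the data are analysed; the article expects collection to end by December 2025.

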### Sample Size Calculation and Power Analysis

According to G*Power 3.1.9.7 [49], when we conducted a power analysis of comparing 2 groups (ie, an intervention group and a control group), an independent *t* test for estimating a sufficient sample size with a 1-tail hypothesis, at a power of 0.80, an alpha level of 0.05, and a medium-large effect size (*d*=0.65-0.70), each group will need to include 26 to 30 participants. The estimated total sample size is 52 to 60 participants. The effect size of 0.65 to 0.70 is based on the large effect sizes (*d*>0.70) of previous internet-based intervention studies [30-35]. When a condition (intervention vs control) is a between-subjects factor and time is a within-subjects factor, a power analysis of a repeated measures within-between interaction (eg, 2 conditions × 3 times) at a power of 0.80, an α level of 0.05, a medium-large effect size (*f*=0.25-0.40), and estimated 8 measures, each group will need to include 8 to 16 participants. The effect size of 0.25 to 0.40 is based on the large effect sizes (ηp^2^>0.14) of previous internet-based intervention studies [30-35]. Therefore, the total sample size of 60 (30 for the intervention group, 30 for the control group) participants is sufficient for the proposed study. In addition, using a wait-list group as a control group is recommended for developmental trials [50].

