**Exclusion criteria**
Godin Leisure-Time Exercise Questionnaire (GLTEQ) score >14 [53]No computer nor mobile device access to the internetPDDS score=7 (ie, using a wheelchair or scooter most of the time) or PDDS score=8 (being bedridden)Anyone living outside of the United StatesAnyone who is unable to speak, read, and write in EnglishNot willing to be randomized to an intervention or control group, complete the surveys and questionnaires, and wear an accelerometer during the intervention periodNo access to reliable internet

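### No listed analysis adjusts for the outcome's baseline value, which costs power in a trial that enrolled 50 of 60; the listed paired t tests should be descriptive only

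*Protocol article*

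**What the plan says.** The Statistical Analysis section states "SPSS 26 (IBM Corp) will be used to conduct descriptive analyses (means, standard deviations), chi-squared tests, independent *t* tests, paired *t* tests", and the same sentence goes on to repeated measures ANOVAs and to 2-way and 3-way mixed ANOVAs. The t tests are given no specific role. The method named for comparing the arms is "We will use 2-way and 3-way ANOVAs to compare measured variables of the intervention and control groups", with condition between subjects and "Time is a within-subjects factor". The surrounding framework is "Our analytic approach will use an intention-to-treat framework, and mixed models will yield unbiased results" under a missing-at-random assumption.

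The Data Collection section makes baseline the first assessment, followed by postintervention, 3 months, 6 months and an optional 12 months. Baseline is therefore available as a level of the time factor. No listed method is described as using it as a covariate.

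The Sample Size section takes the total of 60 from "an independent *t* test for estimating a sufficient sample size with a 1-tail hypothesis", and adds a second calculation for the condition-by-time interaction.

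On entry, the exclusion criteria include "Godin Leisure-Time Exercise Questionnaire (GLTEQ) score >14", and the inclusion criteria also require low recent activity. The GLTEQ is an outcome as well: under Questionnaire Measures, "PA and sedentary behavior will also be assessed using patient-reported scales", one of which is the GLTEQ.

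**The concern.** In a randomised trial with a continuous outcome measured before and after treatment, conditioning on the baseline value gives an arm contrast at least as precise as the follow-up-only or change-score contrast, apart from the one degree of freedom. A follow-up-only t test discards the baseline. A condition-by-time contrast between baseline and one follow-up visit is a comparison of change scores, which subtracts the whole baseline whatever its correlation with the outcome. Below a correlation of 0.5 this is noisier than ignoring baseline altogether.

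The loss matters here because the trial aimed for 60, enrolled 50 and has since lost 7. The data that would recover part of the power are already being collected.

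The secondary concern is the paired t tests. The hypotheses in the Objectives section are that the intervention group will exceed the control group, and a within-arm test cannot address that. Entry also selects people with low activity, so activity scores can rise on retest with no programme effect.

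**Working it through.** **Inputs from the protocol.** d=0.65, the lower end of 0.65-0.70; alpha 0.05; one-tailed (Sample Size section; the Statistical Analysis section gives no sidedness). 25 per arm enrolled, with 3 and 4 dropouts, leaving 22 and 21 (Results).

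**Assumed, not in the protocol.** The baseline-outcome correlation r, taken as 0.5, 0.6 and 0.7, with 0.3 as a low case.

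**The plan's own figure.** A one-sided independent t test with 80% power (noncentral t) needs 29.97 per group at d=0.65 and 25.94 at d=0.70. That is 30 and 26, so the stated 26 to 30 per group is reproduced.

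**Noncentrality at 22 and 21.** Unadjusted: d·√(n1·n2/(n1+n2)) = 0.65·√(462/43) = 2.131, df 41.
- Change score: multiply by 1/√(2(1−r)), which is 1.000, 1.118 and 1.291 at r=0.5, 0.6 and 0.7. This gives 2.131, 2.382 and 2.751, df 41.
- Baseline as covariate (ANCOVA): multiply by 1/√(1−r²), which is 1.155, 1.250 and 1.400. This gives 2.460, 2.663 and 2.983, df 40.

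**Power at d=0.65.**

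| Analysis | Sides | r=0.5 | r=0.6 | r=0.7 |
|---|---|---|---|---|
| Follow-up only | two | 55% | 55% | 55% |
| Change score | two | 55% | 64% | 77% |
| ANCOVA | two | 67% | 74% | 83% |
| Follow-up only | one | 67% | 67% | 67% |
| Change score | one | 67% | 76% | 86% |
| ANCOVA | one | 78% | 83% | 90% |

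At r=0.3 the two-sided figures are 55% follow-up only, 42% change score and 59% ANCOVA.

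**Regression to the mean in a paired t test.** Assume bivariate normal scores, entry below a cut c (in SD units), no true effect, n=25 in an arm and a two-sided 5% test.
- *Screening score reused as baseline.* Spurious rise = (1−r)·φ(c)/Φ(c), where r is now the retest correlation. With an assumed median cut (c=0), φ/Φ = 0.399/0.5 = 0.798. The rise is 0.40, 0.24 and 0.16 SD at r=0.5, 0.7 and 0.8, and the paired test is significant 55%, 34-35% and 24% of the time.
- *Baseline measured again after screening.* Spurious rise = (r_SB − r_SF)·φ(c)/Φ(c), where r_SB and r_SF are the correlations of screening with baseline and with follow-up. If all correlations are equal, the rise is zero and rejection is about 5%. With r_SB=0.8 and the other two correlations 0.7, the rise is 0.1×0.798 = 0.08 SD and rejection about 8%. With r_SB=0.9 and the others 0.7, it is 0.16 SD and about 17%.

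**The case against.** A reader might infer from the list of t tests that efficacy will be judged by them. The protocol does not say so. The t tests stand in an inventory alongside descriptive statistics and chi-squared tests, and the sentence that assigns a method to the arm comparison names the ANOVAs. The only formal role of a t test is in the sample size, where the condition-by-time interaction is powered as well. This objection stands, and the point is confined accordingly.

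Because the interaction does use baseline, the fair comparator for the named analysis is the change score, not the follow-up-only test. Against it the two-sided gain is 12, 10 and 6 points at r=0.5, 0.6 and 0.7, not the full distance from 55%. That also stands. The change-score contrast is valid under randomisation, so the issue is efficiency rather than bias.

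A reader might also suppose that the effect will be read from the condition main effect, which averages in the untreated baseline visit. With four or five visits this would shrink a constant effect by 1/4 or 1/5. The arithmetic is right, but the protocol does not name that term as the efficacy test.

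On the paired tests, every hypothesis is between arms, and regression to the mean cancels between randomised arms in expectation. Nothing says that a within-arm gain will be offered as evidence of efficacy. The 24-55% figures need the screening GLTEQ to serve as baseline, whereas the Recruitment section places the baseline survey after telephone screening. The direct exposure is limited to activity measures, chiefly the GLTEQ; the HAPA scales are not selection variables.

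Finally, an article may leave covariates to a fuller plan. However, this one does name its methods, and the comment is on that choice.

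**Conclusion.** The point holds as an efficiency criticism with a secondary caution. None of the named methods conditions on the outcome's baseline value. At 22 and 21 participants and d=0.65, adding it raises two-sided power from 55/64/77% (change score) or 55% (follow-up only) to 67/74/83%. One-tailed, it rises from 67/76/86% or 67% to 78/83/90%. These figures rest on assumed correlations of 0.5/0.6/0.7, and the gain over a change score grows as the correlation falls.

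The paired t tests do not test the stated hypotheses. Their false-positive rate for the GLTEQ, with an assumed median cut, runs from about 5% if baseline is re-measured with equal correlations to 24-55% if the screening score is reused. The protocol does not settle which applies, so the upper figures should not be quoted as expected. The documents do not support the stronger readings, that efficacy rests on t tests or that within-arm gains will be claimed as programme effects.

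**What to change.** Name one between-arm analysis for each outcome: the arm contrast at the visits that the hypotheses refer to (postintervention and 6 months), estimated either with the outcome's baseline value as a covariate or from a mixed model with a common baseline mean for both arms. The second option fits the mixed-model framework already stated. Report within-arm changes descriptively, without paired t tests as inference. State whether the baseline GLTEQ is the screening score or a fresh measurement.

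The cost is one degree of freedom and a few sentences in the analysis section. No new data are needed. As data collection is still running according to the Results section, the wording should be fixed before outcomes are examined by arm.
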